### Setting, participants, recruitment and randomization

The study will take place at a youth mental health clinic linked to the Brain and Mind Research Institute (BMRI) at The University of Sydney, Australia. The participants will be young people who present to the mental health clinic, who complete a routine clinical “intake” assessment and the treating medical practitioner (usually a psychiatrist) confirms that they meet the eligibility criteria. The treating medical practitioner will then obtain written informed consent from the young person (plus consent of a parent or primary carer for those aged ≤ 16 years) to participate in the YES program.

The inclusion criteria are that the individual is: (i) aged 14–25 years; (ii) has a clinical diagnosis of an anxiety, unipolar, bipolar or psychotic disorder according to *Diagnostic and Statistical Manual of Mental Disorders, version IV* (DSM-IV) criteria [14]; (iii) is willing and able to give independent written informed consent to participate in the study (in addition, parental consent is required for those aged 14–16 years).

The exclusion criteria are that the individual has: (i) a clinically assessed IQ ≤ 70; (ii) a major neurological disorder, a medical illness which impacts on cognition, and/or a history of sustained head injury; (iii) inadequate English language skills to allow participation in groups (or completion of RCT assessment protocols); (iv) a current alcohol or substance misuse disorder and/or an acute psychotic or manic episode that impairs the individual’s ability to give informed consent and/or requires acute clinical treatment; (v) a risk of serious self-harm (as assessed by a medical professional); and/or (vi) participated in a research study of any structured psychological interventions within the preceding 12 months.

Individuals who are eligible for the study will be randomized to start with either: module A (Social Participation) followed by module B (Physical Well-being) or to start with module B followed by module A. An independent person (i.e. a colleague not directly involved with the study) will undertake the randomization using a computerized random number generator program Fig. 1.

**Fig. 1 Fig1:**
[figure not shown]
Recruitment, consent and randomization flowchart

### Measures

There are some resource constraints for this study; hence for the pilot RCT, we will use the clinical assessment of the case (including the DSM-IV diagnosis) provided from the details recorded at intake by the treating medical practitioner. Outcome measures will rely mainly on self-report ratings of progress and outcome, but the treating practitioner, (who is blind to the randomization sequence) will provide an observer rating for the key primary outcome measure (of social and occupational functioning).

We selected ten self-report ratings and one observer-rating scale to measure outcomes associated with each target domain. These research assessment tools are widely used in mental health research and were selected partly because many of them are regarded as “standard” measures of outcomes in community, clinical and research populations and/or they have been found to have acceptable reliability and validity across age groups [5, 10–12]. Furthermore, the BMRI clinical services use many of these ratings routinely. As described in our previous publications, the clinic provides ongoing training and supervision in the use of clinical assessment tools and observer rating scales to ensure inter-rater reliability and consistent use [15].

Measures of outcome are divided into primary and secondary ratings, and the time points for these assessments are shown in Table 1.

**Table 1 Tab1:** Schedule of enrollment, interventions and assessment time points

Phase	Pre-randomization		Post-randomization				Post-trial
Time point	Enrollment	Allocation	week 1	week 8	week 11	week 19	week 52 follow-up
Enrollment	x						
Clinical assessment (including DSM-IV diagnosis by treating medical practitioner)							
Eligibility screen	x						
Informed consent	x						
Randomization		x					
Allocates sequence of modules:							
AB or BA							
1^st^ Module							
2^nd^ Module							
Primary assessments:			x	x	x	x	x
Functioning - SOFAS and FAST							
Symptoms *-* SPHERE12			x	x	x	x	x
Disability *-* BDQ							
Self-esteem - RSEQ							
Vocational status:	x					x	x
Education, employment, receipt of benefits, etc.							
Engagement with intervention:				x		x	
Number of sessions attended							
Secondary assessments:			x	x	x	x	x
Levels of distress *-* K-10							
Social well-being *-* WHOQOL							
Physical health/Lifestyle:			x	x	x	x	x
Sleep profile - PSQI							
Exercise/Activity profile - IPAQ							
Tobacco and substance use *-* ASSIST							
Other measures:	x		x	x	x	x	x
Anthropometrics**:**							
BMI, body weight, waist circumference							
Metabolic screen and other blood tests:	x					x	x
Lipids, fasting glucose, FBC, LFTs, etc.							

*ASSIST* Alcohol, Smoking and Substance Involvement Screening Test, *BDQ* Brief Disability Questionnaire, *BMI* body mass index, *DSM-IV Diagnostic and Statistical Manual of Mental Disorders, version IV*, *FAST* Functional Assessment Short Tool, *FBC* full blood count, *IPAQ* International Physical Activity Questionnaire, *K-10*, Kessler Psychological Distress Scale, *LFTs* liver function test, *PSQI*, Pittsburgh Sleep Quality Index, *RSEQ* Rosenberg Self Esteem Questionnaire*, SOFAS* Social and Occupational Functioning Assessment Scale, *SPHERE 12* Somatic and Psychological Health Report, *WHOQOL* World Health Organization Quality of Life Scale

#### Primary outcome measures

i.Social and Occupational Functioning Assessment Scale (SOFAS): this is an observer-rated instrument that assesses functioning on a scale of 0–100, with lower scales suggesting more severe levels of impairment. The SOFAS is widely used in clinical research and practice and has been used in several research projects with young people that have been undertaken at the BMRI [5, 11, 16].ii.Functional Assessment Short Test (FAST): this is a 24-item self-report measure that examines impairment across 6 domains: autonomy, occupational functioning, cognitive functioning, financial issues, interpersonal relationships and leisure time. It has been used in adults with bipolar disorder, schizophrenia and attention deficit hyperactivity disorder (ADHD) [17, 18]. It has been shown to have good psychometric characteristics with both a reliability and validity of about 0.9 each [18, 19]. This the first study to use the FAST in a population of 14–25 year-olds.iii.Somatic and Psychological Health Report (SPHERE 12): is a 12-item self-report questionnaire which assesses 6 psychological (PSYCH-6) and 6 somatic (SOMA-6) symptoms. This screening tool has been shown to have a reliability of 0.9 a validity of 0.8 in populations aged 16 years and over [20, 21] and is widely used in youth mental health research [22].iv.Brief Disability Questionnaire (BDQ): is an 8-item subjective rating of disability in everyday activities. It has been widely used in adult psychiatric populations [23, 24] and more recently has been used in youth populations [9, 11, 16].v.Rosenberg Self Esteem Questionnaire (RSEQ): is a 10-item self-rated scale designed specifically for use in adolescent populations and has a reliability of 0.9 and a validity of 0.8 [25, 26]. A score representing a global measure of self-worth and for negative and positive self-esteem can be derived.

#### Secondary outcome measures

i. Kessler Psychological Distress Scale (K-10): this is a 10-item version of the Kessler scale that was developed for use in the US National Health Survey Interview (NHIS) and has been employed extensively around the world in (including Australia) across broad age groups in clinical and community settings. The K-10 gives a global measure of distress based on anxiety and depressive symptoms over a 4-week period, with a reliability of 0.9 and a validity of 0.8 [27, 28].

ii. World Health Organization Quality of Life Scale (WHOQOL): this 26-item self-rating gives a summary measure of functioning and social well-being across 4 domains: physical, psychological, social and environmental. It has been used across a wide range of age groups (from 12 to 97 years) and shows very high reliability and validity [29].

iii. Pittsburgh Sleep Quality Index: is a 24-item self-rating that gives a global measure of sleep quality. It assesses seven domains: sleep latency; sleep duration, habitual sleep efficiency, and sleep disturbances, use of sleep medication and daytime dysfunction. In young adult populations (aged 18–32 years) it has been shown to have good psychometric properties with both a reliability and a validity of about 0.8 [30, 31].

iv. International Physical Activity Questionnaire (IPAQ): is a 9-item questionnaire that assesses time spent walking, vigorous and moderate-intense activity, and sedentary activity. The IPAQ has been tested across populations and broad age groups in 12 countries and demonstrates a reliability of 0.8 and validity of 0.6 [32, 33].

v. Alcohol, Smoking and Substance Involvement Screening Test (ASSIST): is a 21-item tool that is used to self-rate current and past use of tobacco, alcohol and other substances. Its reliability is high (0.90) and it has been used worldwide, frequently in youth populations [34, 35].

Other Measures: anthropometric measurements (body mass index (BMI), waist circumference, etc.) and blood for pathology tests (e.g. metabolic and inflammatory markers) are collected routinely at the youth mental health clinic at the BMRI. These routine data and results of tests are reviewed by the treating medical practitioner and repeated as deemed necessary throughout the course of any treatment program [5, 15]. For this study we have added a specific schedule for treating medical staff to repeat these measures to fit with key assessment points in the RCT (see Table 1).

The routine intake assessment also collects data on educational or vocational status, and receipt of benefits. Again we will specifically ask clinicians to record this at selected time points throughout the course of the study.

For the purposes of the study, we will have access to records giving basic details of medication and/or other treatments received and will review these at the beginning of the study, at the end of the YES program, and again at the final follow-up. (However, this information will not be included in the formal analysis as resource constraints prevent us from collating information in sufficient detail to be able to interpret if findings are significant, e.g. differences dosages of medication prescribed, week-by-week medication changes, or levels of adherence, etc.)

### YES intervention

A particular challenge for delivering a psychological intervention in youth is to find non-threatening ways to engage individuals who exhibit different levels of self-confidence and/or vary in their actual levels of social and/or inter-personal skills [10, 11]. Hence, specific behavioral or psychological techniques may be less efficacious if the attendees feel too anxious about their performance on tasks (such as concentration exercises or changing behaviors) to engage in the process and such issues may lead to premature drop-out if the individual begins to feel stressed by participation in the group program. However, if individuals are enabled to overcome these potential barriers, the group format can offer peer support and be a suitable vehicle for delivering a wide range of technologies that increase rather than decrease the chance that the individual will achieve the goals they have set for themselves.

Both the “social” and “physical” modules incorporated in the group intervention are of 8 weeks duration and there are 2 sessions a week that together provide about 4 hours of group work (1 session is slightly longer than the other). This translates as 16 sessions (32 hours) per module – which is in keeping with many complex therapies offered to adults that target a specific major mental disorder (such as cognitive behavioral therapy (CBT) for schizophrenia, group psycho-education for bipolar disorder, and is longer than the interpersonal therapy (IPT) intervention for depression). It is our view that the duration is justified as there are multiple targets for this program, (including mental health, emotional/developmental issues and physical health) and that at this phase of their personal development many young people benefit from additional time to allow them to engage with the therapy and get used to attending the group and then benefit further from repetition of the key learning points through a range of different cognitive, behavioral and social mechanisms and interactive exercises and experiences.

To help foster familiarity with the format of the program, the structure of the session remains relatively fixed throughout the course of each module. However, the content varies from week to week and between modules. A range of different formats and modalities (art work, Internet programs, You-tube or similar open-access videos, phone “apps,” brief interactive group games or exercises) are used to ensure there are opportunities to engage youth with different skills, abilities and preferences and to anchor the learning exercises, (such as cognitive remediation components) to real-world situations.

A trained professional with a specific knowledge and skills facilitates the group on each topic/subject area. For example, “Anxious Art” (Social Participation: module A) is facilitated by an art teacher at the National Art School of Australia, whilst cardio boxing (Physical Well-being: module B) is co-ordinated by an accredited fitness instructor. The maximum group size is 15 young people starting each module (either A or B). Allowing for the small anticipated drop-out rate (estimated from our prior experience), we predict 12-regular attendees per module session. A pilot manual of topics and program content, including resources and teaching aides required, will be updated after the trial and made available.

Feedback by group participants and discussion of learning points with the group leader are often delivered during less formal parts of the session such as during an “afternoon tea and cake” break.

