### Sample size/Power calculation

This feasibility study will allow us to undertake sample size calculations for future multi-center studies and inform the selection of outcome measures. There are no studies that have undertaken group interventions that target the same variables and outcomes specifically as this study and, most importantly, as both modules are deemed “active” interventions, we do not anticipate large between group differences associated with the modules. However, based on previous data from published clinical observational studies and controlled trials (that have estimated means scores on the SOFAS and FAST to be about 60–70 and 20–25 at baseline and clinically significant improvement to be associated with score changes of about 15–25 % over about 10–20 weeks), we have made a conservative estimate that each module can produce a statistically significant improvement in the scores (*p* < 0.05 with > 80 % power) on the 2 most important primary assessments: namely, the continuous measures of functioning (the FAST and SOFAS) of > 5 points between week 1 and week 9, and between week 11 and week 19 (we have not made any predictions associated to the 12-month follow-up).

Randomization of 120 individuals, with predicted retention of about 90–100 individuals at week 8 will give a sample size that is sufficient to detect clinically significant changes in functioning with medium to large effect sizes. Also, we predict this initial recruitment level would provide follow-up assessments on about 72–80 individuals at week 19 and about 66–70 individuals at 12 months.

Information on categorical outcomes (such as vocational status) is likely to be available on a larger sample, as it does not require the individual to participant in self-rated or observer-rated assessments, nor attendance for laboratory tests. Feedback is encouraged by all participants and is included as part of the week-to-week “summary/discussion” at the end of each group session. As such, whilst this information will be used for planning modifications to the programme, it is not being formally collated and analyzed.

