### Statistical analysis plan

All data are entered into and analyzed descriptively using SPSS, version 21 (SPSS Inc., Chicago, IL, USA). As this research was conducted in health service settings (with participants, clinicians and/or administration information being utilized\, there are variable rates of missing data, which will be taken into account in the analysis plan.

Primary analyses will be based on the intention-to-treat (ITT) sample: i.e. everyone who was randomized will be included in the analysis regardless of participation (full or partial or none) in the intervention groups. The primary outcome is the change in FAST (self-rated) and SOFAS (observer-rated) score pre-intervention to post intervention (e.g. between weeks 1–8 and then weeks 11–19). A preliminary analysis will be reported on week-8 outcomes once the target sample has completed this stage.

Further analyses will evaluate the scores at the end of the follow-up period and changes in secondary outcome measures. Categorical outcomes, such as vocational status will be examined using simple (chi-squared) and logistic regression models.

Mixed-model repeated measures analyses may be used for some analyses because of the ability of this approach to include participants with missing data without using discredited techniques such as last observation carried forward.

Additional analyses will include per-protocol analyses and statistical methods to explore factors that moderate outcomes, including attrition rates and, if appropriate, levels of presenting severity associated with significant social, clinical or functional improvement or change in vocational status.

Finally, some basic analyses will be undertaken of anthropometric and metabolic screening data. The latter will include a review of the uptake of these screening tests by study participants, and any barriers to this approach, as well as analysis of the findings. This pilot data will be used to inform power calculations for future studies.

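### The power claim and the named analyses make no allowance for therapy groups of up to 15; any within-group correlation would lower power and understate standard errors

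*Protocol article*

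**What the plan says.** The protocol article, under YES intervention, describes each module as 16 sessions (32 hours) over 8 weeks, delivered in groups. It states that "The maximum group size is 15 young people starting each module (either A or B", and after drop-out "we predict 12-regular attendees per module session". It presents the shared setting as helpful in itself: "the group format can offer peer support and be a suitable vehicle for delivering a wide range of technologies".

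Under Sample size/Power calculation, the estimate is that each module can produce a "statistically significant improvement in the scores (*p* < 0.05 with > 80 % power" on FAST and SOFAS "of > 5 points between week 1 and week 9, and between week 11 and week 19". The supporting numbers are counts of people: "Randomization of 120 individuals, with predicted retention of about 90–100 individuals at week 8". No number of groups, ICC or design effect appears.

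Under Statistical analysis plan, the primary outcome is the change in FAST and SOFAS across each module, with no single test fixed. For other outcomes, "Categorical outcomes, such as vocational status will be examined using simple (chi-squared) and logistic regression models". A mixed-model repeated measures analysis is optional, and the reason given for it is missing data. No therapy-group term is mentioned for any analysis.

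**The concern.** Randomizing individuals does not keep their outcomes independent when treatment is then delivered in groups. Members of one group share peers, sessions and calendar time for 32 hours, and the article itself counts peer support as a potential benefit. Module A works on social participation, and the two lead outcomes measure social and occupational functioning, so some positive within-group correlation in change is plausible.

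If it is present, a group of 12 carries less information than 12 independent people. The stated power is then too high, and any test or interval that ignores group is too optimistic. The article also says this trial will supply sample-size inputs for later multi-center studies, so understated standard errors and a missing ICC would carry forward.

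**Working it through.** **Inputs from the article.** Up to 15 starters per group and 12 regular attendees (YES intervention). 120 randomized, 90–100 at week 8, p < 0.05, power above 80%, and a change of more than 5 points within each module (Sample size/Power calculation).

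**Assumptions.** Two-sided alpha of 0.05; 1:1 allocation, so 45–50 per sequence at week 8; ICC of change 0.02, 0.05 or 0.10. The article gives neither an ICC nor an SD of change.

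**1. The plan's own figure.** Without an SD, the claimed power cannot be reproduced. What can be found is the largest SD of change at which 5 points has 80% power if participants are independent:

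SD_max = 5 × √n / (1.960 + 0.842)

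- n = 45: 5 × 6.708 / 2.802 = 12.0 points
- n = 50: 5 × 7.071 / 2.802 = 12.6 points

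**2. Number of groups.** 120 / 15 = 8 groups in the first period at the fewest, or 4 per sequence. With 45–50 analysed per sequence, that is 45/4 to 50/4 = 11.3 to 12.5 per group, so m = 12 is a fair working value.

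**3. Design effect and its consequences.** DE = 1 + (m − 1) × ICC, with m = 12.

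- Size of a nominal 5% test: 2 × [1 − Φ(1.960/√DE)]
- Power where 80% was planned: Φ(2.802/√DE − 1.960)
- SD_max with clustering: (12.0 to 12.6)/√DE

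| Assumed ICC | DE | √DE | Size of 5% test | Power (nominal 80%) | Effective n from 90–100 | SD_max for 5 points |
|---|---|---|---|---|---|---|
| 0 | 1.00 | 1.00 | 5.0% | 80% | 90–100 | 12.0–12.6 |
| 0.02 | 1.22 | 1.10 | 7.6% | 72% | 74–82 | 10.8–11.4 |
| 0.05 | 1.55 | 1.24 | 11.5% | 61% | 58–65 | 9.6–10.1 |
| 0.10 | 2.10 | 1.45 | 17.6% | 49% | 43–48 | 8.3–8.7 |

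The last column addresses the claim the article makes, which is about change within each module. The proportional loss, 1/√DE, is the same whatever n is used.

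**4. Few groups.** The table uses normal critical values. With 4 groups per sequence, a comparison between sequences has about 8 − 2 = 6 group-level degrees of freedom, and a change within one sequence about 4 − 1 = 3. At ICC 0.05, nominal 80% power then becomes about 47% (6 degrees of freedom) or 35% (3 degrees of freedom), using the noncentral t distribution. This is the pessimistic end, because it takes the fewest possible groups and places all degrees of freedom at group level.

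**The case against.** The strongest reply has four parts.

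- **The analysis is not fixed.** A reader might infer that the plan commits to independence-based tests for FAST and SOFAS. It does not: no test is named for the primary change, and the optional mixed model could hold a group term, as could a logistic model. A condensed article may leave random effects and degrees of freedom to an analysis plan that is not shown. This stands for the primary outcomes. It does not rescue the power statement, which is made here. Nor does it help the chi-squared test, which is named and has no place for a group effect.
- **The ICC is unknown.** A reader might infer that standard errors are certainly too small and that type I error does exceed 5%. Both depend on an ICC above zero, and the documents give none. This stands, so every figure above is conditional.
- **Facilitators.** A reader might infer that each group has its own therapist. The article assigns professionals by topic and never says that they differ between groups of the same module. Facilitators who serve all groups would add no between-group variance. This stands, and the argument here rests only on shared peers, sessions and timing.
- **Exploratory purpose.** The article calls the study a feasibility and exploratory trial. That lowers the stakes, but it still makes a formal power claim and intends the results to inform future sample sizes.

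**Conclusion.** The concern holds in conditional form. The power statement counts individuals and makes no visible allowance for treatment delivered in groups, and the named analyses carry no therapy-group term. At 12 per group and an ICC of 0.02 to 0.10, nominal 80% power would be about 72% down to 49%. An analysis ignoring group would run a nominal 5% test at about 7.6% up to 17.6%. The 5-point within-module claim would need an SD of change no larger than about 11.4 points at the mild end and 8.3 at the severe end, against 12.0–12.6 under independence. Few groups make this worse.

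These sizes rest on an assumed ICC, two-sided tests and equal allocation. The documents do not support saying that the primary analysis is wrong as specified, because it is not specified to that level. The change should be made, but the point does not invalidate the design.

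**What to change.** 1. Record group membership separately for the first and second module. Recruitment was already underway when the article was written, and this information is harder to recover later.
2. Analyse change in SOFAS and FAST with a period-specific random effect for module group, using Kenward-Roger or Satterthwaite degrees of freedom.
3. For vocational status at weeks 19 and 52, each person may by then have belonged to two different groups, so a single group intercept is not enough. Use a cross-classified mixed logistic model, or cluster-robust errors with a small-sample correction, allowing for both groupings, in place of a simple chi-squared test.
4. In the sample-size section, give the expected number of groups and restate power or detectable change over a stated ICC range, or say plainly that the figure does not allow for clustering.
5. Report the estimated ICC with its interval, since later trials will need it.

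The cost is one group-identity field per module, some added wording, wider intervals and a lower quoted power. No extra participants are required.
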